### Study design

2.1

This study is a fully blinded two-armed pragmatic RCT, which will be executed in the Netherlands implemented at multiple physical or exercise therapy clinics. The study consists of three in-clinic assessments performed by participants’ own therapists (Figure 2). After a baseline assessment (T0), participants will start with a 6-week usual care control period, followed by a midterm assessment (T1). Subsequently, participants will undergo 2 weeks of in-clinic familiarization and training with Strolll AR supervised by their therapist. Then, participants will start with the 6-week Strolll AR intervention at home integrated with usual care, followed by the final in-clinic assessment (T2).

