**Figure 2 fig2:**
[figure not shown]
Schematic of the study design.

The definition of a pragmatic RCT is that the intervention is tested in a real-world population in a real-world setting (i.e., the clinic), with an appropriate comparison arm (i.e., usual care alone in the current study) and relevant outcomes to determine its effectiveness (24, 25). Special trial designs can be considered. In this particular pragmatic RCT, all participants follow the same T0-control-T1-intervention-T2 procedure, suitable for both between-groups and within-subjects comparisons of the Strolll AR intervention effects as well as for evaluating its clinical feasibility. With regard to the between-groups comparison, participants will be allocated to control (using T0-T1 change data) or intervention (using T1-T2 change data) groups using multiple (*n* = 20) two-armed randomizations following a 1:1 ratio (Figure 3). The randomization will be predefined by an independent person using a Matlab (26) script (see Supplementary material S5), locked with a date and timestamp, and kept concealed from participants, therapists, and researchers. After the final T2 assessment of the last participant, the 20 randomizations of participants over control and intervention groups will be revealed to the researchers and applied in the data analysis (as detailed in section 2.7.3). Participants, therapists, and researchers will therefore all be blind to group allocation during the study, which is impossible for rehabilitation interventions with traditional RCT or cross-over designs. Note that a longitudinal design with a fixed order for all participants may be prone to time-dependent confounding factors, such as progressive worsening of Parkinson’s disease symptoms over time. We would like to emphasize that potential time effects associated with disease progression work conservatively against finding intervention effects. This particular pragmatic RCT design is not recommendable for situations where conditions improve over time (e.g., natural recovery after acute stroke), as this would promote arbitrary intervention effects associated with natural improvement in conditions over time. This design, in which all participants receive the Strolll AR intervention, further allows for a complementary within-subjects evaluation of the intervention effect (i.e., being less susceptible to between-subjects variation than aforementioned between-groups evaluation), while at the same time providing ample information on the clinical feasibility of the Strolll AR platform implemented in the clinical pathway in terms of its safety, adherence, performance, and user experience (i.e., from both participants’ and therapists’ perspectives), making efficient use of scarcely available resources (e.g., funding limiting scientific staff, time limiting availability of clinical staff, patients limiting the number of participants). Moreover, a design with the same procedure for all participants makes implementation of this study in the clinical pathway easier (hence the term pragmatic RCT) and potentially reduces the dropout rate because no participants are withheld from receiving the intervention due to the randomization.

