#### Usual care (6-weeks)

2.2.3

During the usual-care control period, participants will not receive any additional training or instructions related to the Strolll AR intervention. In line with the pragmatic nature of the trial, participants will, however, continue with their weekly therapy schedule with their therapist, as provided prior to the study. The therapists involved are affiliated with the ParkinsonNet network (Dutch society for Parkinson’s therapists (36) and deliver therapy following the Dutch physiotherapy guidelines for Parkinson’s disease (1).

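### The study is labelled fully blinded, but only the analysis allocation lists are concealed; treatment is open and the assessors are unmasked

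*Protocol article*

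**What the plan says.** All of the following is in the protocol article.

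- **The label.** Section 2.1 opens with "This study is a fully blinded two-armed pragmatic RCT".
- **The blinding claim.** After the Figure 2 caption, section 2.1 adds "Participants, therapists, and researchers will therefore all be blind to group allocation during the study", and says that traditional RCT or cross-over designs cannot achieve this for rehabilitation interventions.
- **What is concealed.** The 20 randomizations are prepared by an independent person, "locked with a date and timestamp, and kept concealed from participants, therapists, and researchers". On timing: "After the final T2 assessment of the last participant, the 20 randomizations of participants over control and intervention groups will be revealed".
- **Order of treatment.** "all participants follow the same T0-control-T1-intervention-T2 procedure". In the usual-care period, "participants will not receive any additional training or instructions related to the Strolll AR intervention" (section 2.2.3).
- **Who assesses.** "The study consists of three in-clinic assessments performed by participants’ own therapists" (section 2.1). Sections 2.2.2, 2.2.4 and 2.2.7 have the therapist administer TUG, FTSTS, 10MWT and Mini-BESTest at T0, T1 and T2. The therapist also supervises familiarization (2.2.5), and prescribes and adjusts the home exercises (2.2.6).
- **FES-I.** Self-reported: filled out by the participant at home at T1 (2.2.4), and with the researcher by telephone at T2 (2.2.7).
- **Contrast.** Section 2.7.3 compares T0-T1 change (Control) with T1-T2 change (Intervention).

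**The concern.** Blinding is meant to stop knowledge of treatment from influencing effort, encouragement, scoring and self-report. The lists hidden here do not determine what anyone receives or how anyone is measured. They only select which of two already recorded changes will be used. At each assessment the participant, the therapist and the researcher know which period has just ended.

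At stake is what the result can support. A reader who takes the label at face value would think that expectation and assessor effects had been controlled by design. The only order-related threat that section 2.1 discusses is time-dependent confounding such as disease progression, which it says works against finding an effect. Expectation and assessor effects would be expected to work the other way, in favour of Strolll AR, and are not mentioned.

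**Working it through.** **1. What each person knows at each assessment**

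| | T1 | T2 |
|---|---|---|
| Period just ended | Usual care, no Strolll AR | Strolll AR, in clinic and then at home |
| Known to participant, therapist and researcher? | Yes (same order for all) | Yes |
| TUG, FTSTS, 10MWT, Mini-BESTest administered by | Own therapist | Own therapist, who prescribed the programme |
| FES-I | Self-report at home | Self-report by telephone with researcher |
| Analysis list known? | No | No |

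Only the last row is masked.

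**2. How a bias enters the contrast.** Score each change so that improvement is positive. Let e0, e1 and e2 be the average expectation or assessor effect at T0, T1 and T2.

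- Control change = true control change + (e1 − e0)
- Intervention change = true intervention change + (e2 − e1)
- Intervention − Control = true difference + (e2 − 2·e1 + e0)

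An effect of constant size at all three assessments cancels. An effect b present only at T2 (e0 = e1 = 0, e2 = b) adds exactly b. The list does not appear in the expression: every T1-T2 change carries b whichever list is drawn, so averaging over 20 lists leaves it in place.

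A simulation agrees. It used 70 completers, SD 3.4 s, zero true effect and 20 random 1:1 splits.

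| Assumed bias in T1-T2 change | Average estimated difference | Splits with p < 0.05 |
|---|---|---|
| 0 | 0.06 s | 5% |
| 1.0 s | 0.97 s | 22% |
| 1.5 s | 1.51 s | 45% |

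**3. The plan's own figure.** Section 2.4 gives d = 0.755 (2.57 s / 3.4 s = 0.756), two-sided alpha 5% and power 80%. The two-sample t-test with the noncentral t gives n = 28.53, rounded up to 29 per group and 58 in total, with power 0.807. The stated sample size reproduces, and this point does not depend on it.

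**4. Illustrative false-positive rates.** Inputs:

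- Group size: 29 per group (section 2.4), and 35 per group, inferred from 100 recruited less about 10 + 10 + 10 losses, giving 70 completers split 1:1.
- Bias: b in SD units of the change score. These sizes are assumptions; the protocol gives none.
- True effect zero, a single split, two-sided 5% t-test.

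The noncentrality is b × √(n/2), with 2n − 2 degrees of freedom. For b = 0.3 and n = 35 it is 0.3 × √17.5 = 1.255, against a critical value of 1.995 on 68 df, and the rejection probability is 0.236.

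| Assumed shift | On TUG, if the SD of change is 3.4 s | 29 per group | 35 per group |
|---|---|---|---|
| 0 | 0 s | 5% | 5% |
| 0.1 SD | 0.34 s | 7% | 7% |
| 0.2 SD | 0.68 s | 12% | 13% |
| 0.3 SD | 1.02 s | 20% | 24% |
| 0.5 SD | 1.70 s | 46% | 54% |

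**The case against.** The strongest reply is that the blinding sentence is literally true. It speaks of group allocation, the lists really are concealed until data collection ends, and section 2.1 describes both the mechanism and the use of participants' own therapists openly. Nothing is hidden and the procedures do not contradict each other. This stands, and it is why qualifying the sentence is enough. It does not rescue the unqualified label, or the claimed advantage over traditional designs, which has value only if knowledge of treatment is masked.

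A reader might go further and infer that concealment achieves nothing. The document does not support that: concealment prevents participants from being handled according to their label, and prevents choice of a favourable split.

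A reader might also infer that the therapist performs every outcome measure. The therapist administers four of the five; FES-I is self-reported.

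The primary TUG, the FTSTS and the 10MWT are timed, and therapists are trained in administering the tests (section 2.3). Both limit discretion in measurement. The training is for interrater reliability, however, not masking, and timed performance still responds to effort and encouragement. Using participants' own therapists follows from the pragmatic design, and no objection is made to that choice here.

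Finally, nothing in the protocol supports a bias as large as 0.5 SD on a timed test. That would be 1.70 s, about two thirds of the 2.57 s target (1.70 / 2.57 = 0.66). The percentages are scenarios, not estimates.

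**Conclusion.** The concern holds as a misdescription of the design. The protocol claims full blinding; what it has is concealment of analysis lists in an open-label study with unmasked assessors. All five effectiveness outcomes are exposed, and a bias specific to T2 passes one for one into the Control-versus-Intervention contrast under all 20 randomizations.

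The size of any such bias is unknown. Over an assumed range of 0.1 to 0.5 SD, the single-split false-positive rate runs from about 7% to 54% at 35 per group (inferred), and from 7% to 46% at 29 per group. These figures assume zero true effect and a shift at T2 only. They do not show that the trial's result will be biased by any given amount. Nor can it be assumed that evidence reviewers will grade the trial as low risk, since section 2.1 tells them who performs the assessments. The correction should be made because the stated property is absent and bears on what the trial may conclude.

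**What to change.** 1. In section 2.1, replace the fully blinded label with: *open-label with unblinded assessors; analysis allocation lists concealed until the last T2*.
2. Qualify the later blinding sentence in section 2.1 so that it claims only that the analysis allocation is concealed from participants, therapists and researchers. Drop the comparison with what is impossible in traditional designs.
3. Add a limitation: expectation and assessor bias favouring Strolll AR cannot be excluded. This applies most of all to the rated Mini-BESTest and the self-reported FES-I, and effort and encouragement can also affect the timed tests.

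The cost is wording only, with no new data and no change to procedures or analysis. The downside is the loss of a favourable design label. The rewording makes the claim accurate; it does not reduce the bias itself.

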
**Figure 3 fig3:**
[figure not shown]
Flowchart from enrollment to statistical analysis.

### Procedure and outcomes

2.2

After enrollment, the study consists of three in-clinic assessments spread out over 14 weeks, demarcating a usual-care control period and a Strolll AR intervention period (Figure 2). Below we describe the procedure for each of these parts of the design.

#### Participant enrollment (C1, C2): enrollment and informed consent

2.2.1

The therapist will inform eligible participants about the study. If people are interested, they will receive a flyer with instructions on how to send their contact details to the researchers. Upon receival of contact details of a potential participant, the researcher will call this person to provide more information about the study (C1, Figure 3). Hereafter, potential participants will receive the participant information letter by mail or email. A week after receiving the participant information letter, the researcher will again call the potential participant (C2, Figure 3) to answer any questions and to ask if he or she wants to participate. If so, in- and exclusion criteria will be checked by the researcher (to the extent possible, otherwise criteria will be evaluated during the baseline assessment session T0). Furthermore, the potential participant will be informed that the medication should remain stable during the study. If the potential participant is eligible, he or she will be asked to sign the informed consent form (see Supplementary material S1), after which the researcher also signs the informed consent form and notifies the therapist that the person can start with the pragmatic RCT. Written informed consent must be given before commencing with the baseline assessment (T0).

#### Baseline assessment (T0): characterization and effectiveness

2.2.2

The baseline assessment serves to characterize the study sample and to provide baseline values for evaluating the effectiveness of Strolll AR (see also Table 1). Study parameters used to characterize the participants are demographics (i.e., age, gender, disease duration) and current medication use [i.e., the Levodopa Equivalent Daily Dose (LEDD)]. Questionnaires to describe the participant population are the Montreal Cognitive Assessment [MoCA; (27), lower scores reflect cognitive decline], Movement Disorders Society Unified Parkinson Disease Rating Scale [MDS-UPDRS; (28), higher scores reflect more severe impairment], New Freezing of Gait Questionnaire [NFOGQ; (29), non-zero scores define freezers], Physical Activity Scale for the Elderly [PASE; (30), higher scores reflect greater self-reported physical activity], and 12-month falls history. All these outcomes will be collected using online questionnaires, except for the MoCA and MDS-UPDRS part Ia, III, and IV, which will be administered in the clinic by the therapist. To be able to evaluate the potential effects of Strolll AR for improving indicators of gait, balance, and falls risk, the following standard clinical tests will be administered by the therapists: Timed Up-and-Go test [TUG; (31), in seconds; a faster completion time reflects better performance], Five Times Sit-to-Stand test [FTSTS; (32), in seconds; a faster completion time reflects better performance], 10-meter walk test [10MWT; (33), in seconds; a faster completion time reflects better performance] and Mini Balance Evaluation Scale Test [(Mini-BESTest; (34), higher scores reflect better performance]. In addition, participants will fill out the Falls Efficacy Scale International [FES-I; (35), higher scores reflect higher concern of falling].

**Table 1 tab1:** Overview of T0, T1, and T2 tests and questionnaires to characterize the study sample and to evaluate the effectiveness and clinical feasibility of the Strolll AR intervention.

	T0	T1	T2
Study sample characterization			
Demographics (age, gender, disease duration)	X		
LEDD	X		
MoCA	X		
MDS-UPDRS	X		
NFOGQ	X		
PASE	X		
12-month falls history	X		
Effectiveness			
TUG*	X	X	X
FTSTS	X	X	X
10MWT	X	X	X
Mini-BESTest	X	X	X
FES-I	X	X	X
Clinical feasibility			
Falls history during usual-care and intervention periods		X	X
Strolll AR evaluation questionnaire			X
UEQ			X
Technology acceptance and use questionnaire			X
Top-3 barriers and facilitators of Strolll AR			X

LEDD, Levodopa Equivalent Daily Dose; MoCA, Montreal Cognitive Assessment; MDS-UPDRS, Movement Disorders Society Unified Parkinson Disease Rating; NFOGQ, New Freezing of Gait Questionnaire; PASE, Physical Activity Scale for the Elderly; TUG, Timed Up-and-Go test; FTSTS, Five Times Sit-to-Stand test; 10MWT, 10-meter walk test; Mini-BESTest, Mini Balance Evaluation Scale Test; FES-I, Falls Efficacy Scale International; UEQ, User Experience Questionnaire. *Primary outcome measure.

#### Usual care (6-weeks)

2.2.3

During the usual-care control period, participants will not receive any additional training or instructions related to the Strolll AR intervention. In line with the pragmatic nature of the trial, participants will, however, continue with their weekly therapy schedule with their therapist, as provided prior to the study. The therapists involved are affiliated with the ParkinsonNet network (Dutch society for Parkinson’s therapists (36) and deliver therapy following the Dutch physiotherapy guidelines for Parkinson’s disease (1).

#### Midterm assessment (T1): effectiveness

2.2.4

For the midterm assessment, the standard clinical tests of gait, balance, and falls-risk indicators (TUG, FTSTS, 10MWT, Mini-BESTest) (Table 1) will again be administered by the therapist. In addition, the participants are asked to fill out the FES-I and 6-week falls history (to assess falls during the usual-care period) questionnaires at home (Table 1).

#### Practice with Strolll AR intervention supervised in clinic (2 weeks)

2.2.5

To make the participant familiar with the Strolll AR platform technology and procedures and to allow the therapist to evaluate safety aspects, the Strolll AR intervention starts with 1 to 3 supervised in-clinic sessions of (cueing-assisted) personalized AR exercises.

In these supervised sessions in the clinic, the therapist will also test and validate procedures to select and tailor effective assistive AR cues from a library of different AR cues (see Supplementary material S2 for the types of cues used in this study). This is needed for two reasons: (1) to test the premise that a one-size-fits-all cue does not exist as there is heterogeneity in the effect of cues among participants, (2) to ensure that the Strolll AR gait-and-balance exercises can be effectively assisted with personalized cues for those who need it (e.g., people experiencing freezing of gait or people with small steps and shuffling gait (16–18)). The so-obtained best cues for supporting gait, as evaluated subjectively using both the participant’s experience and the therapist’s impression, will be used during the remainder of the Strolll AR intervention for those who are deemed to benefit from it. We will document if AR cues are added to Strolll AR gait-and-balance exercises, and when applicable, specify the type of AR cues as well as their personalized parameters (intercue distance, height, width, audiofeedback, etc.).

To deliver the Strolll AR intervention, participants in this study will by default be equipped with Magic Leap 2 AR glasses for its unmatched vertical AR field of view. Special insert lenses from a complementary lens kit (supports 8 prescriptions from −2.0 to +3.0) made available at each clinical site will be used to correct vision for people wearing spectacles. In case vision cannot be corrected with these insert lenses (e.g., due to a special prescription not part of the lens kit), either tailored insert lenses will be ordered for Magic Leap 2 or Microsoft HoloLens 2 with a slightly smaller vertical AR field of view will be used which can be worn over spectacles to deliver the intervention.

Once the participant is deemed sufficiently capable of using the Strolll AR platform technology independently at home in a safe manner (after training in the clinic with the therapist for one to maximally three sessions of 1 hour in 2 weeks), the participant will take the AR glasses home together with a complementary SIM-card equipped WiFi router to continue the Strolll AR intervention independently at home. If the Strolll AR intervention at home is not deemed safe or suitable by the therapist, the intervention will stop and the reason for this will be documented by the therapist as part of the clinical feasibility evaluation.

#### Training with Strolll AR intervention independently at home (6 weeks)

2.2.6

The Strolll AR intervention, integrated with usual care, comprises of a 6-week home-based individualized AR gait-and-balance exercise program assisted with tailored AR cues when deemed beneficial. The AR exercises are designed to train aspects associated with gait, balance, and falls risk in a gamified manner to maximize training compliance. Strolll AR comprises seven AR exercises, namely Basketballl, Smash!, Mole Patrolll, Hot Buttons, Puzzle Walk, Wobbly Waiter, and Cue Challenge (Figure 4; see Supplementary material S2 for a detailed description of all AR exercises), intended to improve gait, balance, and falls risk in people with Parkinson’s disease. Exercises that require walking have optional complementary AR cueing (Smash!, Cue Challenge), integrated cueing (speed cue in Wobbly Waiter) or AR-mediated goal-directedness (the moles in Mole Patrolll, the puzzle pieces in Puzzle Walk), to various degrees enabling and assisting people with more severe mobility impairments to participate. For each AR exercise, feedback of performance in terms of game-play performance metrics and functional performance metrics are given during the exercises. For Basketballl, for example, metrics associated with the number of balls thrown in the basket (game-play performance) and the number of sit-to-stands or squats made (functional performance) are given, derived from AR glasses data. See Supplementary material S2 for more details on the AR exercises, metrics, and types of cues.

**Figure 4 fig4:**
[figure not shown]
Strolll AR gait-and-balance exercises: Smash! [without **(A)** and with **(B)** assistive AR cues], Mole Patrolll **(C)**, Hot Buttons **(D)**, Basketballl **(E)**, Puzzle Walk **(F)**, Wobbly Waiter **(G)**, and Cue Challenge **(H)**.

Participants will be invited by their therapist to use Strolll AR minimally 5 times a week for 30 active minutes per day, resulting in the recommended 150 minutes per week (1, 7, 8). They can perform the exercises anytime during the day, in one bout or in multiple chunks during the day, with complementary AR cueing when deemed beneficial. The precise exercises, exercise duration, difficulty level, and order will be prescribed by the therapist via the Strolll web portal (Figure 5). Therapists were by default recommended to prescribe all AR exercises, as each AR exercise targets different aspects (see Supplementary material S2). However, they were allowed to make adjustments, if necessary, to align with the participant’s abilities and needs, as well as for practical considerations. The prescribed exercises will be evaluated and adjusted on a weekly basis in telephone calls, e-consults or during an onsite therapy session using information of the participant in combination with the feedback from exercises that are reported in the Strolll web portal, such as adherence and game-play and functional performance metrics (cf. Supplementary material S2). Adherence will be defined as the percentage of performed over prescribed gait-and-balance exercises [i.e., both frequency and session-duration adherence; (15)]. The data on game-play level and performance will be used to evaluate whether the exercise program was both progressive (increase in level) and achievable (consistently high game-play performance scores) as intended. The weekly contact moments with the therapist will also be used to ask if participants experienced any adverse events (safety flags). Specifically, safety will be evaluated as the number of adverse events due to the Strolll AR intervention, such as falls, dizziness, eye strain, and headache. Potential technical issues will be documented by the researcher, who will be available to provide technical support during the study based on email or telephone contact with the participants.

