#### Final assessment (T2): effectiveness and clinical feasibility

2.2.7

To be able to evaluate the effectiveness of the Strolll AR intervention, the therapist will again administer standard clinical tests of gait, balance, and falls risk (TUG, FTSTS, 10MWT, Mini-BESTest). Participants will fill out the FES-I questionnaire together with the researcher during a telephone call (Table 1).

Clinical feasibility of the Strolll AR platform according to the participants will be assessed in terms of user experience [i.e., the User Experience Questionnaire (UEQ); (37)], technology acceptance and use [i.e., questionnaire based on the Unified Theory of Acceptance and Use of Technology model (UTAUT; (38))], top-3 barriers and facilitators of Strolll AR, and intervention-specific questions regarding Strolll AR, including cueing if used during the intervention (see Supplementary material S3). Participants will also report their falls history during the intervention period. The questionnaires of the final assessment are completed through a telephone call with the participant to ensure comprehensibility, which was first assessed in think-aloud sessions with a number of participants (39). In light of the potential future implementation in the clinical pathway, therapists will also be asked about their experience with Strolll AR through a purpose-made questionnaire (see Supplementary material S4), including the technology acceptance and use questionnaire, the top-3 barriers and facilitators (assessed before training their first participants and after training their last participant), and the UEQ (assessed after their last participant completed the study). Furthermore, a focus group with the therapist will be organized after the study for an in-depth evaluation of the top-3 barriers and facilitators.

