#### Feasibility (safety, adherence, performance, and user experience)

2.7.2

Clinical feasibility will be evaluated on several aspects. First, to determine if the Strolll AR intervention can be safely performed at home, descriptive outcomes will be reported for safety (i.e., number of dropouts during training at home including the reasons for withdrawal, adverse events including a paired-samples *t*-test comparison of the average weekly number of falls experienced during usual-care and intervention periods), providing insight into the potential risks of the Strolll AR intervention.

Second, to determine if the Strolll AR intervention was adherable over the course of the intervention, we will conduct a repeated-measures one-way ANOVA with the within-subject factor Time (three levels) on adherence scores derived from the first, second, and third part of the intervention at home (i.e., default intervention period is 6 weeks, so adherence is derived over roughly two-weeks intervals). The assumption of sphericity will be checked according to Girden (43). If Greenhouse–Geisser’s epsilon exceeds 0.75, the Huynh-Feldt correction will be applied; otherwise, the Greenhouse–Geisser correction will be used. Effect sizes will be quantified with *η*_p_^2^. Paired-samples *t*-tests will be used for post-hoc comparisons of a significant main effect of Time. In addition, one sample *t*-tests against 100% will be performed for adherence scores at each Time point to determine whether or not there were systematic deviations from the prescribed treatment.

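### For adverse events other than falls, the safety outcome keeps only those attributed to Strolll AR, and no usual-care count is stated to set beside them

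*Protocol article*

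**What the plan says.** Section 2.2.6, on home training, describes how events are elicited: "The weekly contact moments with the therapist will also be used to ask if participants experienced any adverse events (safety flags"). The next sentence defines the outcome: "safety will be evaluated as the number of adverse events due to the Strolll AR intervention, such as falls, dizziness, eye strain, and headache". So the question is open to any event, while the stated outcome keeps only those attributed to the device.

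Falls have a second, separate route:
- At T1 (section 2.2.4) participants complete a "6-week falls history (to assess falls during the usual-care period) questionnaires at home".
- At T2 (section 2.2.7): "Participants will also report their falls history during the intervention period".
- Table 1 has a row for "Falls history during usual-care and intervention periods", marked at T1 and T2.
- Section 2.7.2 plans a paired t-test, a "comparison of the average weekly number of falls experienced during usual-care and intervention periods", with no condition on cause.

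Section 2.7.2 also reports dropouts during home training with their reasons.

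Neither section 2.2.4 nor Table 1 mentions dizziness, eye strain, headache or other events for the usual-care period. Therapist contact does exist in that period, because participants "continue with their weekly therapy schedule with their therapist, as provided prior to the study".

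**The concern.** Dizziness and headache also occur in people who wear no device. When such a symptom arises during home training, someone must decide whether the glasses caused it. The blinding described in section 2.1 covers only the concealed analysis randomizations. Every participant follows the same fixed order, so participant and therapist both know when Strolll AR is in use.

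The error can go either way. If events are put down to Parkinson's disease or medication, the count is too low. If background symptoms are blamed on the glasses, it is too high. A usual-care count would show roughly how much symptom burden to expect without the device. The design gives every participant such a period, and the authors use it for falls, but the article states no equivalent for the other three harms it names.

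Feasibility is a primary study parameter in the abstract, with safety listed first among its components. Section 2.7.2 uses the safety results to judge whether home use is safe.

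**Working it through.** **The plan's own figures.** No safety figure is stated. The only computed figure is the sample size for TUG in section 2.4. It reproduces: 2.57 / 3.4 = 0.756, and a two-sample t-test with d = 0.755, two-sided alpha of 5% and 80% power needs 28.53, so 29 per group and 58 in total. This point does not affect it.

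**What is collected, by harm**

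| Harm named in 2.2.6 | Usual care | Home period | Comparison stated |
|---|---|---|---|
| Falls | Falls history at T1 | Falls history at T2, plus weekly question | Paired t-test, all falls |
| Dizziness | None stated | Weekly question; counted if due to Strolll AR | None |
| Eye strain | None stated | As dizziness | None |
| Headache | None stated | As dizziness | None |

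Three of the four named harms thus have no stated control-period count.

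**An inconsistency for falls.** Section 2.2.6 lists falls among the events counted when due to Strolll AR. Section 2.7.2 compares all falls. The two can give different numbers of falls for the same period, and the text does not say which is the reported safety result.

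**Size, by assumption only.** From section 2.4:
- Home users: 100 − about 10 usual-care dropouts − about 10 exclusions before home use = about 80.
- Completers: 80 − about 10 further dropouts = about 70.

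Expected participants with a given symptom and no device effect = n × assumed 6-week prevalence:

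| Assumed prevalence | n = 80 | n = 70 |
|---|---|---|
| 5% | 4 | 3.5 |
| 10% | 8 | 7 |
| 20% | 16 | 14 |
| 30% | 24 | 21 |

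Now suppose that prevalence is 20% without the device and 30% with it. Among 80 users, 0.30 × 80 = 24 report the symptom and (0.30 − 0.20) × 80 = 8 are excess. If between 10% and 70% of the 24 are attributed to the device, the attributed count runs from 2.4 to 16.8, that is, about 2 to 17 around a true excess of 8.

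**What a control count would add.** With 70 participants observed in both periods and the same assumed 20% and 30%, the 95% half-width of the within-person difference is 1.96 × √[(0.2×0.8 + 0.3×0.7 − 2ρ√(0.16×0.21)) / 70]. This is 0.142 for ρ = 0 and 0.101 for ρ = 0.5. A 10-point difference would be estimated to within about 10 to 14 points: useful as description, not a sharp test.

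**The case against.** A reader might infer that the trial has no background rate for safety at all, or that the whole safety result rests on unblinded attribution. The document does not support this. Falls, the first harm named, are compared between periods within person and regardless of cause. Dropouts with reasons are reported, and the weekly question covers any event, so unattributed events may well be on record.

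It can also be said that the article condenses a fuller protocol. Recording windows and causality rules are commonly left to that document, and Table 1 lists tests and questionnaires rather than the weekly question. This has force. The absence of an attribution rule is not held against the plan here, and the article does not say that symptoms go unrecorded during usual care. What remains is the outcome rule that section 2.2.6 does state, together with a T1 assessment whose listed safety content is falls alone.

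Further, non-fall events are only described, with no test or threshold, and a device-related count is a legitimate descriptive outcome. That is so, but a descriptive count used to judge safety still needs something to be read against. Finally, a control-period count would not remove the problem: reporting stays unblinded to period and the order is fixed. That stands, and it limits what the remedy can deliver.

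**Conclusion.** The point holds for adverse events other than falls. Their stated outcome keeps only events attributed to Strolll AR, although any event is asked about, and no usual-care collection is stated. The resulting count depends on unblinded attribution and has no background rate. Falls do not share this weakness, though sections 2.2.6 and 2.7.2 should be reconciled on which falls are counted.

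The extent is three of the four named harms, plus unnamed non-fall events. The numerical size is unknown. The 4 to 24 background reporters and the 2-to-17 range follow wholly from assumed rates and should not be read as estimates for this trial. Only the 80 home users and 70 completers derive from the article, and those are approximate. The conclusion also assumes that the full protocol adds no symptom recording in usual care. The effectiveness analysis and the sample size are untouched.

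**What to change.** 1. **Main safety table.** Report the number and percentage of participants with each adverse event (falls, dizziness, eye strain, headache, other) regardless of cause. Keep events judged due to Strolll AR as a secondary column.
2. **Same question in both periods.** Ask one short fixed question at existing usual-care contacts as well as in the home period, or at minimum use the same checklist at T1 and T2, and report by period. The study runs 6 + 2 + 6 = 14 weeks, so a T2 checklist should refer to the 6 home weeks if the windows are to match.
3. **Participants already past T1.** Section 2.3 puts the start of recruitment in May 2024 and the last T2 in February 2025, so control-period symptoms can no longer be collected prospectively for many or all participants. For them, report every event recorded at the weekly contacts, whatever its attribution, and state that non-fall events have no control-period comparison.
4. **Wording.** Align sections 2.2.6 and 2.7.2 on whether the reported falls are all falls or attributed falls.

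The cost is a little therapist time, some data entry, one table and more non-serious events on record. A T1/T2 checklist also relies on 6-week recall, which weekly questioning avoids. The comparison between periods stays unblinded and in fixed order, and should be described that way.
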